**Inclusion and exclusion criteria**

To be included in EOS study, patients must meet all the following inclusion criteria:

- Patients having signed written informed consent
- Males and females aged 18-70 years
- Diagnosis of PMS
- EDSS ≤6.5
- Female patients Not pregnant
- No contraindications to MRI

Exclusion criteria

- HIV positivity
- severe renal, hepatic, oncological, hematological and psychiatric diseases

No data will be collected for patients with even only one of the above-mentioned conditions not respected.

**Early discontinuation of patients**

A subject may withdraw from the study at any time at his/her request, at the discretion of the investigator for safety, behaviour, or administrative reasons.

## DATA MANAGEMENT AND STATISTICAL METHODS

**Data collection and data entry**

All the clinical data will be collected and saved in Red Cap by the personnel from the two centers. Red Cap will be accessible to the Data Management and statistician staff where the data entry, data cleaning and quality control activities will be organized.

Query will be raised if one or more data are unclear or contradictory.

**MedDRA Dictionary**

Medical events reported as Comorbidities and Complications will be classified using the last available version of the Medical Dictionary for Regulatory Activities (MedDRA), an international medical terminology dictionary applied by regulatory authorities and by pharmaceutical industries. The three levels of codes (SOC – PT – LLT) will be implemented into the database.

**Statistical analysis**

All collected data will be analyzed using descriptive statistics. Continuous variables will be described with number of patients with valid observations, mean, standard deviation, median, minimum and maximum value. If necessary, additional descriptive statistics may be calculated (in particular, for non-normally distributed data, the median with interquartile range). Categorical data will be described by frequencies and related percentages within variable. A p-value of 0.05 will be used as the cut off for statistical significance (no statistical test will be used for safety data).

Any comparisons between pre- and post- changes in continuous variables will be evaluated with paired sample t-test or Wilcoxon signed rank-test, as appropriate.

In particular, all safety and efficacy data will be analyzed using descriptive statistics. Safety data will be assessed by reporting and describing all the adverse events. Decisions following the safety pattern will be discussed by the study investigators, but no logic based on statistical test was set.

Depending on the results of interest, a stratified or an exploratory analysis may be conducted.

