| **Methods** | Patients meeting all inclusion/exclusion criteria will be included in the study after having provided their written informed consent.  They will undergo two pre-treatment assessments: at -6 months (-6M) and at baseline visit (M0) and two post-treatment assessments at month 1 (M1), and at month 6 (M6).  The treatment will consist in the oral administration of a minimum dosage of 5 grams per day of Forza, provided in the form of capsules. Each capsule will contain approximately 0.7g of Forza. The capsules will be administered as follow: 4 capsules in the morning and 3 additional capsules in the evening from baseline () to month 6 (M6).  At each timepoint the following assessments will be evaluated: electrophysiological (motor evoked potentials – MEPs; somatosensory evoked potentials – SEPs; visual evoked potentials – VEPs), optical coherence tomography (OCT), and neurofilaments (NfL).  In addition, clinician assessed outcomes (CAO), patient reported outcomes (PRO) and performance measure (PF) will be acquired for the motor domain (Expanded Disability Status Scale – EDSS; Timed 25 Foot Walk - T25FW; 12-item Multiple Sclerosis Walking Scale - MSWS12; Nine-Hole Peg Test - 9HPT), for the cognitive domain (Montreal Cognitive Assessment - MOCA; Symbol Digit Modalities Test - SDMT), for the emotional domain (Hospital Anxiety and Depression Scale - HADS), and for the bladder domain (Overactive Bladder - OAB).  Brain MRI will also be obtained at each timepoint as standard of care procedure.  In order to investigate the potential effect of Forza on brain metabolism (concentration of glutamate, N-acetylaspartate, creatine, choline) and microstructure, a subgroup of 25 patients (enrolled at the University of Genoa) will undergo MRI with a multi-shell diffusion-weighted (DWI) sequence and proton magnetic resonance spectroscopy (1H-MRI) in addition to routine sequences. |
| **Endpoints** | The primary outcome of the study will be safety, and the co-primary efficacy outcome will be a reduction in the NfL change over 1 and 6 months as compared to the pre-treatment NfL change. |
| **Statistical analysis** | The NfL percentage changes will be compared pre and post treatment within patients by a non-parametric paired Wilcoxon test. |
| **Expected results** | We expect to verify the safety of an add-on therapy with *Forza* in PMS and to obtain clinical, paraclinical and laboratory information on the effects of *Forza* in this condition. |
|  |  |

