**Secondary objectives**

Secondary objectives of the study are:

- Exploring the clinical and biological efficacy of Forza in PMS both after one month and six months of treatment or at the end of the study (in case of early withdrawal).

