## METHODS

**Study design**

This is a prospective, multicenter, single-arm non-interventional study. It consists of a first visit six months before the assumption of osmotin (-6M), in which the investigators will inform patients about the study design and objective and the possibility to take part of it.

Then, only after having obtained a written informed consent, demographics characteristics and info about MS history will be collected, and clinical evaluations and assessments will be performed.

During a subsequent baseline visit, six months after the first one, (0M) the same clinical evaluations and assessments will be performed and after their execution the treatment will be administered and taken by the patients.

Two post treatment follow up visits are planned at 1 month (1M) and six months (6M) after the baseline, in which the same clinical evaluations and assessments will be recorded.

Patients meet all inclusion/exclusion criteria will be included in the study after having provided their written informed consent.

They will undergo two pre-treatment assessments: at -6 months (-6M) and at baseline visit (M0) and two post-treatment assessments at month 1 (M1), and at month 6 (M6).

The treatment will consist in the oral administration of Forza capsules at a minimum dosage of 5 grams per day.

At each timepoint the following assessments will be evaluated:

- Electrophysiological (motor evoked potentials – MEPs; somatosensory evoked potentials – SEPs; visual evoked potentials – VEPs)
- Optical coherence tomography (OCT)
- Neurofilaments (NfL)

In addition, clinician assessed outcomes (CAO), patient reported outcomes (PRO) and performance measure (PF) will be acquired for investigating the following domains:

- Motor domain (Expanded Disability Status Scale – EDSS; Timed 25 Foot Walk - T25FW; 12-item Multiple Sclerosis Walking Scale - MSWS12; Nine-Hole Peg Test - 9HPT)
- Cognitive domain (Montreal Cognitive Assessment - MOCA; Symbol Digit Modalities Test - SDMT)
- Emotional domain (Hospital Anxiety and Depression Scale - HADS), and for the bladder domain (Overactive Bladder - OAB).

Brain MRI will also be obtained at each timepoint as standard of care procedure.

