In order to investigate the potential effect of Forza on brain metabolism (concentration of glutamate, N-acetylaspartate, creatine, choline) and microstructure, a subgroup of 25 patients (enrolled at the University of Genoa) will undergo MRI with a multi-shell diffusion-weighted (DWI) sequence and proton magnetic resonance spectroscopy (1H-MRI) in addition to routine sequences.

Any changes on disease modifying therapy (DMT), any occurrence of adverse events during treatment period and any interruption of treatment will be recorded on the medical chart.

[figure not shown]

[figure not shown]

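### One unadjusted 0.05 significance cut-off covers every non-safety pre/post comparison of a continuous variable, although efficacy is called exploratory and is to be analysed descriptively

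*Supplement*

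**What the plan says.** Under Statistical analysis the protocol sets a single threshold: "A p-value of 0.05 will be used as the cut off for statistical significance (no statistical test will be used for safety data". The next sentence gives the test: "Any comparisons between pre- and post- changes in continuous variables will be evaluated with paired sample t-test or Wilcoxon signed rank-test, as appropriate". Safety is the only exemption. No list of tested variables, testing order or multiplicity adjustment is given, and nothing says that p-values outside NfL are nominal.

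The same section also says: "In particular, all safety and efficacy data will be analyzed using descriptive statistics". The Secondary objectives read "Exploring the clinical and biological efficacy of Forza in PMS both after one month and six months of treatment", and the synopsis likewise describes the efficacy aim as exploratory.

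NfL stands apart. The synopsis states that "the co-primary efficacy outcome will be a reduction in the NfL change over 1 and 6 months as compared to the pre-treatment NfL change" and names a paired Wilcoxon test for it. The sample size is built on NfL alone.

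The other outcomes are named under Study design:
- "Electrophysiological (motor evoked potentials – MEPs; somatosensory evoked potentials – SEPs; visual evoked potentials – VEPs"
- "Optical coherence tomography (OCT"
- four motor, two cognitive, one emotional and one bladder instrument
- brain MRI
- an imaging substudy: "In order to investigate the potential effect of Forza on brain metabolism (concentration of glutamate, N-acetylaspartate, creatine, choline) and microstructure, a subgroup of 25 patients"

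**The concern.** A purely descriptive analysis needs no significance cut-off. The section gives both instructions and does not say which governs. An analyst who follows the threshold sentence literally may call any secondary p-value below 0.05 statistically significant. With many outcomes and two post-treatment visits, some such results are expected by chance alone.

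The study has one arm, so no concurrent control group helps a reader discount them. The dissemination plan foresees conference presentations. What is at stake is whether an isolated secondary result can be reported as a significant change on Forza without the reader knowing how many comparisons were made.

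**Working it through.** **The plan's own figure.** The documents state no number of tests and no family-wise error rate, so there is nothing to reproduce. The count below is a reconstruction.

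**Count of named outcomes other than NfL (Study design).** 3 evoked-potential measures + 1 OCT + 4 motor (EDSS, T25FW, MSWS12, 9HPT) + 2 cognitive (MOCA, SDMT) + 1 HADS + 1 OAB + 1 brain MRI + 4 metabolites + 1 microstructure = 18. At two visits, 18 × 2 = 36. The flow chart leaves motor evoked potentials unmarked at 1 month, which gives 35.

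**Count by flow-chart rows.** SEPs and VEPs have no row, and the substudy imaging is a single row. Eleven rows are marked at both visits (OCT, EDSS, T25FW, MSWS12, 9HPT, MOCA, SDMT, HADS, OAB, brain MRI, substudy MRI) and MEPs at 6 months only: 11 × 2 + 1 = 23.

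**Expected false positives under no effect.** k × 0.05 gives 23 × 0.05 = 1.15 and 36 × 0.05 = 1.80. These do not depend on correlation.

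**Chance of at least one false positive.** Assumptions: two-sided tests (the plan does not say), every null hypothesis true, and an equal correlation ρ between all test statistics. The documents give no correlations, so a range is shown. With c = 1.96 and φ, Φ the standard normal density and distribution function:
- Independent, either direction: 1 − 0.95^k. This is 1 − 0.95^23 = 0.693 and 1 − 0.95^36 = 0.842.
- Independent, favourable direction only: 1 − 0.975^k. This is 0.441 and 0.598.
- Correlated, either direction: 1 − ∫[Φ((c − √ρ·w)/√(1−ρ)) − Φ((−c − √ρ·w)/√(1−ρ))]^k φ(w) dw. For the favourable direction only, the second Φ term is dropped.

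| Assumed ρ | Either direction, k = 23 | Either direction, k = 36 | Favourable only, k = 23 | Favourable only, k = 36 |
|---|---|---|---|---|
| 0 | 69% | 84% | 44% | 60% |
| 0.5 | 45% | 55% | 23% | 28% |
| 0.8 | 24% | 27% | 12% | 14% |

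**A second correlation structure.** For 35 tests, take a correlation of 0.5 between the two visits and 0, 0.3, 0.5 or 0.7 between outcomes. The either-direction chance is then 81%, 73%, 60% and 45%; the favourable-only chance is 56%, 41%, 32% and 23%.

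**NfL itself.** The synopsis sets NfL change over both 1 and 6 months. Two independent tests at 0.05 give 1 − 0.95² = 9.8%.

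**The case against.** The strongest reply is that the plan does not treat these outcomes as confirmatory. The objectives speak of exploring, efficacy data are to be described, and no sentence says that a significant secondary result establishes an effect of Forza. Many statisticians would not require family-wise control for exploratory outcomes in a 50-patient single-arm study. The 0.05 is a per-test cut-off, so no stated family-wise alpha is exceeded. No separate analysis plan is among the documents, and multiplicity detail is often left to one.

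Most of this stands. It rules out treating the point as a failed confirmatory analysis, and it makes mandatory adjustment debatable. It does not remove the conflict inside the Statistical analysis section, which is about a rule that is written down, not about detail left for later. The authors considered what should not be tested and exempted safety only. The section also mentions an exploratory analysis separately, as something optional, so the pre/post tests are not labelled exploratory where they are defined.

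A reader might also infer that about 35 secondary tests are each to be declared significant, and that a false Forza effect is therefore more likely than not. The documents do not support that. They commit to no list, and they limit the named tests to continuous variables. EDSS is ordinal, brain MRI and microstructure name no measure, and SEPs and VEPs are absent from the flow chart. In the other direction, MEPs, OCT and MRI can each yield several variables. A false claim of benefit also needs a favourable result, and its chance passes 50% only for the larger count with tests close to independent.

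**Conclusion.** The point holds as a weakness of reporting and interpretation. As written, the 0.05 rule can label chance findings as significant, and the plan gives the reader no means of discounting them. On a reconstructed 23 to 36 tests, 1.2 to 1.8 false positives are expected under no effect. The chance of at least one in either direction is well above 5% throughout the range examined (24% to 84%).

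Whether it exceeds one half depends on correlations that the documents do not give, so an unconditional statement that a false effect is more likely than not is not justified. For a favourable false result the range is 12% to 60%, and at correlation 0.5 it is 23–28%. All these figures assume two-sided tests and no true change in any outcome.

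**What to change.** In the Statistical analysis section:

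1. Restrict the 0.05 significance claim to the NfL efficacy outcome. Name which of the 1-month and 6-month contrasts carries it, or split alpha between the two. The naming is needed because the synopsis gives both times and calls NfL co-primary, while the objectives place all efficacy under secondary.
2. For all other outcomes, state that results are given as mean or median differences with 95% confidence intervals and labelled exploratory, that any p-value is nominal, and that none is described as statistically significant.
3. List the variables compared and report how many comparisons were made. A multiplicity-adjusted p-value alongside the nominal one is optional.

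The cost is a few sentences of protocol wording; no data collection or design element changes. The downside is that fewer secondary results can be called significant.

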## PLAN FOR DISSEMINATION OF STUDY RESULTS

Upon completion of data collection and statistical analysis, a final report, including a review of the methods and objectives, together with presentation and discussion of results, will be drawn.

Results of the study will be presented at national and international conferences.

